## Abstract

**Background:**

People with intermittent claudication are at increased risk of death from heart attack and stroke compared to matched controls. Surgery for intermittent claudication is for symptom management and does not reduce the risk of cardiovascular morbidity and mortality. Increasing physical activity can reduce claudication symptoms and may improve cardiovascular health. This paper presents the pilot study protocol for a randomised controlled trial to test whether a brief psychological intervention leads to increased physical activity, improvement in quality of life, and a reduction in the demand for surgery, for patients with intermittent claudication.

**Methods/Design:**

We aim to recruit 60 patients newly diagnosed with intermittent claudication, who will be randomised into two groups. The control group will receive usual care, and the treatment group will receive usual care and a brief 2-session psychological intervention to modify illness and walking beliefs and develop a walking action plan. The primary outcome will be walking, measured by pedometer. Secondary outcomes will include quality of life and uptake of surgery for symptom management. Participants will be followed up after (a) 4 months, (b) 1 year and (c) 2 years.

**Discussion:**

This study will assess the acceptability and efficacy of a brief psychological intervention to increase walking in patients with intermittent claudication, both in terms of the initiation, and maintenance of behaviour change. This is a pilot study, and the results will inform the design of a larger multi-centre trial.

**Trial Registration:**

Current Controlled Trials ISRCTN28051878

## Background

Patients with Peripheral Arterial Disease (PAD) have been described as 'a high risk, but neglected, disease population' [1]. The disease is common in older adults, has serious health implications, but is not as intensively treated as other cardiovascular diseases [2]. PAD is caused by atherosclerosis in the leg arteries, which leads to a reduction in blood supply to the lower limbs. The most common symptom of PAD is intermittent claudication (IC), leg pain when walking. The prevalence of PAD increases with age, Fowkes et al [3] found that 4.5% of 55 to 74 years olds had IC in the Edinburgh Artery Study, with prevalence increasing to over 20% of over 75 year olds [4].

Atherosclerotic build-up on the walls of arteries is not confined to one part of the arterial system, therefore a diagnosis of IC is an indicator of atherosclerosis in other parts of the body. Indeed, patients diagnosed with IC are at increased risk of cardiovascular co-morbidity and mortality. Caro et al [5] analysed a large database of patients with PAD and found that 33% of patients with PAD died, mainly from cardiovascular events, within 5 years of diagnosis of IC. A diagnosis of IC can therefore be seen as an important early warning sign of future cardiovascular problems, and should trigger measures to reduce the risk of death and vascular co-morbidity [6].

Many of the risk factors for atherosclerosis are behavioural, and include smoking, lack of physical activity, high cholesterol levels, high blood pressure, diabetes and obesity. Treatment for patients diagnosed with IC includes risk factor modification and surgery. Walking benefits patients with PAD as it reduces blood pressure, improves the lipid profile of the blood, and encourages development of a collateral blood supply [7]. In a Cochrane review of exercise for intermittent claudication, Leng et al [8] found significant improvements in walking distance following exercise therapy, the most effective exercise regimens involving walking to near-maximal pain, three times a week. Leng called for further research to determine the degree of supervision required in an exercise programme, and how long changes in exercise could be expected to last following participation in an exercise programme.

At present in the UK, supervised exercise programmes for patients with IC are relatively uncommon, therefore exercise for claudication is usually promoted by advice alone. Stewart & Lamont [9] indicated a number of reasons why advice alone may not be appropriate for patients with IC, including patients' loss of confidence/self-efficacy in their ability to walk, their embarrassment at having to stop and rest, and their concerns that pain may be an indication that walking is harmful to them. The aim of this RCT is to test a brief psychological intervention designed to improve walking in patients with IC.

In our recent qualitative study of factors associated with walking in patients with IC, we found that two belief systems influenced walking - (1) beliefs about the illness, and (2) beliefs about walking [10]. We found that patients with claudication tended to have a poor understanding of the causes of their illness, the health consequences of their illness, or the benefits of walking either to their general health or to reduce claudication symptoms.

While some previous studies using brief psychological interventions to increase physical activity in populations at high risk of developing cardiovascular disease have had disappointing results e.g. [11-13], the present study differs because (i) the intervention is designed to address the barriers to walking particular to patients with IC, whereas other studies have included heterogeneous groups of patients facing a wide range of unknown barriers to physical activity; (ii) the patients included in this study have sought treatment for their disease and are therefore presumably more motivated to adhere to treatment than patients being offered unsolicited interventions to increase physical activity; (iii) this study will objectively directly measure behaviour change, in the form of mean daily steps as measured by pedometer, rather than relying on self-report measures of physical activity, or objective measures of fitness as a proximal measure of behaviour change; (iv) this study will measure all outcomes at three time points, 4 months, 1 year and 2 years from baseline, thereby distinguishing between initiation and maintenance of behaviour change - previous studies have not tended to measure all outcomes at all time points and therefore cannot distinguish between the initiation and maintenance of behaviour change.

### Framework

Our intervention was designed using the MRC Framework for the development and evaluation of complex interventions to improve healthcare [14]. We identified existing evidence for the benefit of walking therapy to patients with claudication, and have conducted a qualitative study to identify key psychological constructs associated with walking in claudicants. Our theoretical framework is based around Leventhal et al's [15] Common-sense model of self-regulation of health and illness (CSM), a dynamic model which considers both the role of illness representations and treatment representations in an individual's coping actions. The CSM suggests that patients' illness representations are based on beliefs about the causes of the illness, how long the illness will last, whether the illness is curable, and the perceived consequences of the illness. Treatment representations can be characterised using the same framework as illness representations - behavioural actions have an identity (e.g. the name of the action), time lines (e.g. the length of time the behaviour will take to achieve the goal, and when and for how long the behaviour has to be carried out), consequences (e.g. outcome expectations about the consequences of the behaviour; judgement about the risk of performing the action), causes (e.g. the mechanism by which the coping action will work) and control (e.g. whether the action will cure or control symptoms or the underlying disease; the individual's beliefs about their ability to carry out the behaviour). The model proposes that the content of these representations determines the cognitive and behavioural actions which the individual will take to cope with the illness. We have identified evidence-based behaviour-change techniques successfully used in other interventions to modify the psychological constructs highlighted in the CSM [16].

This trial is a pilot to test whether a brief psychological intervention to modify these constructs can lead to an increase in walking in IC patients. In the pilot study we will test recruitment and retention rates, preliminary efficacy of the intervention at both short and long-term follow-up, acceptability of the intervention, and acceptability of pedometers as a way of measuring walking behaviour in this patient group. The results from this pilot trial will provide an effect size to inform the power and sample size calculations for a larger, multi-centre trial.

### Trial objectives

To examine whether:

• a brief psychological intervention can improve walking and quality of life for patients with intermittent claudication;

• a brief psychological intervention can reduce the demand for surgery for symptom management;

• improvement in walking is mediated by changes in illness and walking beliefs;

• participation in the intervention improves surgical outcomes e.g. walking behaviour and quality of life, for participants who have surgery.

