### Usual Care

Participants in the intervention group and control condition will receive usual care while participating in the study. All participants will be diagnosed as having intermittent claudication by the Vascular Assessment Nurse, who provides all patients with an information sheet about Peripheral Arterial Disease and advises patients to 'stop smoking and start walking'. All participants then attend an outpatient clinic to meet with a Vascular Surgeon, who will discuss appropriate treatment with the patient. Appropriate treatment depends on the age and health of the patient, the size and location of the narrowing of the artery, and on the patient's wishes. If the patient chooses surgical intervention they will then be put on a waiting list for surgery or angioplasty. Approximately 56% of patients diagnosed with IC in NHS Forth Valley proceed to receive angioplasty or surgery, usually within 6 months of diagnosis. If the patient chooses conservative treatment, they will be invited to attend a further outpatient clinic in 3 months time, and then discharged if their claudication symptoms remain stable. Patients who receive angioplasty are followed up by the surgeon for 1 year and then discharged; patients who receive surgery are followed up by the surgeon for 5 years.

At the time of 4 month follow-up in the RCT, all patients will have attended the outpatient clinic to meet the Vascular Surgeon, and a treatment decision will have been made. However, patients will be on a waiting list and will not have received treatment.

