### Analysis

Data will be analysed using an intention to treat protocol in a repeated measures mixed design (2 groups*2 time points for short-term outcome, and 2 groups*4 time points for long-term outcome). Our aim is to determine the effect size achieved by this pilot to inform the sample size calculation for a larger, multi-centre study. Between-group differences in uptake of surgery will be measured using a chi-square test.

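### The fourth objective asks a causal question only in participants who have surgery, a group formed after randomisation that the intervention is meant to change, so it should be labelled exploratory and non-randomised

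*Protocol article*

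**What the plan says.** The Trial objectives section lists four questions. The fourth is whether "participation in the intervention improves surgical outcomes e.g. walking behaviour and quality of life, for participants who have surgery". The second is whether "a brief psychological intervention can reduce the demand for surgery for symptom management".

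The abstract treats surgery as an outcome: "Secondary outcomes will include quality of life and uptake of surgery for symptom management". The Analysis section compares it between arms: "Between-group differences in uptake of surgery will be measured using a chi-square test". For the main outcomes the same section states: "Data will be analysed using an intention to treat protocol in a repeated measures mixed design". It names no method for the fourth objective.

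The Usual Care section describes how patients come to surgery: "Appropriate treatment depends on the age and health of the patient, the size and location of the narrowing of the artery, and on the patient's" (the sentence closes with what the patient wants). It gives the local rate: "Approximately 56% of patients diagnosed with IC in NHS Forth Valley proceed to receive angioplasty or surgery, usually within 6 months of diagnosis". On the position at the 4-month visit it says: "However, patients will be on a waiting list and will not have received treatment".

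**The concern.** The fourth objective is worded causally (the intervention *improves* outcomes) and fixes its population as those who have surgery. Membership of that group is decided after randomisation and after the intervention has been delivered. It depends partly on the patient's own preference, which an intervention aimed at beliefs about illness and walking could plausibly shift. The second objective expects such a shift.

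If the shift occurs, the operated participants in the intervention arm are a different selection of patients from those in the control arm. A difference in their later walking or quality of life could then reflect who was operated on, what the intervention did, or both. The intention-to-treat statement does not repair this, because the objective itself restricts the population. As the pilot is also meant to supply effect sizes for a larger trial, a confounded estimate could be carried forward as if it were a treatment effect.

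**Working it through.** **1. Order of events.** By the Usual Care section, participants still await any procedure at the 4-month visit. The two sessions and the 6- and 12-week calls are over by then. Surgery therefore follows both randomisation and intervention, and outcomes after surgery can be seen only at the 1- and 2-year visits.

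**2. The objectives side by side.**

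| Objective | Population | Protected by randomisation? |
|---|---|---|
| Walking and quality of life | All randomised | Yes |
| Demand for surgery (chi-square) | All randomised | Yes |
| Outcomes in those who have surgery | Selected after randomisation | Only if the intervention does not alter who is operated on |

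Equal uptake in the two arms would not prove that the condition in the last row holds, since the mix of patients could still differ.

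**3. The plan's own sample size.** For a 2 × 2 group-by-time interaction, λ = f²·N·m/(1−ρ), with f = 0.2, m = 2 and α = 0.05. The article does not give ρ. Assuming ρ = 0.5, N = 52 gives power 80.7%, which reproduces the stated 26 per condition. (ρ = 0.3 would need 72 in total, and ρ = 0.7 would need 32.)

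**4. Size of the surgical subset.** 60 recruited − 6 dropouts = 54, or 27 per arm. 27 × 0.56 = 15.1, so about 15 per arm if uptake is equal.

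- Standard error of a difference, 15 v 15: √(1/15 + 1/15) = 0.37 SD. The 95% half-width is 2.048 × 0.365 = 0.75 SD.
- Difference detectable with 80% power: about 1.06 SD (15 v 15).
- Power for the plan's f = 0.2 at N = 30, again with ρ = 0.5: about 57%.

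**5. Illustration of the bias, on assumptions only.** Suppose surgery follows a normal liability correlated r with severity, and the intervention has no effect on outcome. Mean severity among those operated on at uptake p is r·φ(z)/p, where z is the cut-off exceeded with probability p. The ratio φ(z)/p is 0.704 at 56%, 0.966 at 40% and 1.159 at 30%.

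| Assumed intervention-arm uptake (control 56%) | Severity gap, r = 0.5 | Severity gap, r = 0.7 | False gap in step *level* if severity correlates −0.5 with steps |
|---|---|---|---|
| 40% | 0.13 SD | 0.18 SD | 0.07 to 0.09 SD |
| 30% | 0.23 SD | 0.32 SD | 0.11 to 0.16 SD |

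The reduced uptakes and all the correlations are assumed; only the 56% comes from the article.

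**6. Set against the noise.** Subsets would be 15 v 11 (27 × 0.40 = 10.8) or 15 v 8 (27 × 0.30 = 8.1). The standard errors are √(1/15 + 1/11) = 0.40 SD and √(1/15 + 1/8) = 0.44 SD. The largest false gap is 0.16/0.44, or about 0.4 of one standard error.

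**7. Level versus change.** Step 5 concerns level. The only repeated-measures design stated is a group-by-time contrast, which compares change from baseline. A severity difference that moves baseline and follow-up steps equally cancels there. Bias remains if severity, or whatever else drives selection, predicts change. Nothing in the article gives the size or sign of that.

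**The case against.** The best case against the point is that the article poses a question and specifies no analysis for it. A condensed article may leave the estimation and labelling of a secondary objective to a fuller plan. The study is a pilot, the sample size rests on the primary outcome, and no power is claimed for the surgical subset. The illustrated bias is small against the noise, and the all-randomised comparison is already the main analysis.

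Much of this stands. The absence of a method is not the fault, and neither is the small subset. What remains is that the objective itself fixes a population selected after randomisation and attaches a causal verb to it. Nothing in the article marks it as exploratory.

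Three stronger readings are tempting, and the documents do not support them:

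- *That the second and fourth objectives undermine each other.* They do not. Uptake of surgery is compared between the arms as randomised and remains a valid comparison.
- *That the bias is known to run against the intervention because its surgical patients would be more severe.* Usual Care lists age, health, lesion and preference as drivers of treatment. Older age or poorer health could steer patients away from surgery, so the direction is open.
- *That the SD figures above measure the bias in the planned analysis.* They rest on assumed inputs and on level, not change.

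**Conclusion.** The point holds as a limit on what one objective can conclude. If the intervention changes who has surgery, the arms within the surgical subset are not comparable by randomisation, and a difference there cannot be read as an effect of the intervention. If it does not, the subsets stay comparable in expectation, but the trial cannot assume so while testing the opposite.

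The size and direction of the bias cannot be derived from the documents. With about 15 operated participants per arm, which assumes 10% attrition and 56% uptake in both arms, imprecision is likely to outweigh it. The primary outcome, the sample size, the uptake test and the walking and quality-of-life comparison in all participants are untouched. The change is worth making because it costs almost nothing and prevents a causal claim that the design does not support.

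**What to change.** - Reword the fourth objective as: describe walking and quality of life after surgery by arm. Label it exploratory and non-randomised.
- Add a table of baseline steps, baseline quality of life and ABPI by arm among operated participants. All three are already collected.
- Adjust any estimate for these baseline values, and state that adjustment removes only measured imbalance.
- Draw causal conclusions about walking and quality of life only from all randomised participants.

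The cost is one reworded objective, one descriptive table and the loss of a causal claim for this subset. No additional data, visits or participants are needed.

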## Methods/Design

### Recruitment

Participants will be recruited from the Intermittent Claudication Outpatient Clinic in NHS Forth Valley. This is a nurse-led clinic which diagnoses people with IC. People are referred from GPs based in Forth Valley. At diagnosis, the Vascular Assessment Nurse will invite consecutive patients to take part in the trial. In order to check representativeness of the participants who agree to take part in the trial, the Vascular Assessment Nurse will ask for verbal consent to retain all patients' age, gender and Ankle Brachial Pressure Index information, whether they agree to participate in the trial or not.

Currently 200 patients are diagnosed each year in the Forth Valley Intermittent Claudication clinic. A sample size calculation carried out using GPower3 [17], indicates that to carry out a (2) group by (2) time mixed ANOVA to detect a small effect size (0.2) with an alpha of 0.05, and a power of 80%, the trial would require 26 participants in each condition. A small effect size of 0.2 was selected in the sample size calculation based on a previous study of an exercise program for physical activity in patients with IC which measured walking outcomes using pedometers [18]. The sample size calculation was based on the conservative initial (2) time point (baseline to 4 month) mixed ANOVA to increase the likelihood that the study was adequately powered to identify an initiation of walking behaviour change. A (4) time point mixed ANOVA sample size calculation required fewer participants in the study, and therefore the larger, initial (2) time point, more conservative sample size calculation was used. The sample size calculation was based on changes in the primary outcome measure. As this is a pilot study, a further aim is to determine the effect sizes achieved in the secondary outcome measures, to help inform the sample size calculation for a larger, more definitive study. Based on a previous study with patients from this population recruited at outpatient clinic, we estimate that 25% of people may decline to participate in the study. Likely attrition rate from the study for this population is unknown, therefore we have estimated a 10% attrition rate during the trial. We therefore aim to invite 80 patients to participate in the trial, of whom we expect 60 to agree to participate, and a further 6 to drop-out during the course of the trial. Based on typical numbers presenting at the clinic who are diagnosed with claudication, recruitment is estimated to take place at the rate of 2 participants/week.

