### Inclusion Criteria

Patients presenting to the Forth Valley Vascular Outpatient Clinic, newly diagnosed with IC in one or both legs will be recruited into the study. A diagnosis of lower limb arterial disease causing intermittent claudication will be established by a vascular assessment nurse or consultant surgeon. This will be based on a combination of investigations including post-exercise ABPI of below 0.9 [6], and duplex ultrasound, magnetic resonance angiography (MRA) or computerised tomography angiography to provide an anatomic view of the arteries.

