### Exclusion Criteria

We will only exclude people who are unable to give informed consent (e.g. due to dementia) or for whom it may be medically unadvisable to increase their daily walking, including patients with heart failure, cancer, patients who cannot walk unaided or patients with a history of orthopaedic surgery which affects walking. Patients with an ABPI of less than 0.35 will also be excluded as they are likely to be offered emergency surgery.

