### Design

This is a pilot randomised controlled trial with patients newly diagnosed with IC randomly allocated to one of two groups. Allocation to group will be carried out by the researcher, who will use a computer generated random number table for allocation (http://www.randomizer.org/). The computer generated random number table was created at the start of the study by a research colleague, who is not involved in participant recruitment or allocation. The researcher will assign consecutive participant numbers to patients as their names are sent to her by the Vascular Assessment Nurse, each participant number will then correspond to a treatment group as established in the computer generated random number table. The researcher will therefore assign participants to groups before she has made any contact, and before she has received any information about them other than their name and phone number. Participants allocated to the control condition will receive usual care. Participants allocated to the intervention group will receive usual care and a brief, 2-session psychological intervention. The Vascular Assessment Nurse who provides usual care at diagnosis, and who recruits participants, will be blind to participant allocation to groups. Other clinical staff in contact with participants during their care, e.g. Vascular Technologists and Vascular Surgeons will be blind to participant allocation to groups. A CONSORT flowchart of the trial design is shown in Figure 1.

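### Surgery uptake is compared only by an unadjusted chi-square test although age and ABPI are held from diagnosis; a prespecified adjusted estimate would remove avoidable imbalance error at little cost

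*Protocol article*

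**What the plan says.** All references are to the protocol article.

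- **Outcome.** The Abstract (Methods/Design) states: "Secondary outcomes will include quality of life and uptake of surgery for symptom management". Reducing demand for surgery is also one of the Trial objectives. The Recruitment section adds that the pilot should yield effect sizes for the secondary outcomes, to help size a larger study.
- **Analysis.** The Analysis section fixes the method: "Between-group differences in uptake of surgery will be measured using a chi-square test". No covariate is mentioned.
- **Baseline data.** The Recruitment section has the nurse retain "age, gender and Ankle Brachial Pressure Index information", subject to verbal consent. The stated purpose is limited: "In order to check representativeness of the participants who agree to take part in the trial".
- **Blinding and allocation.** The Design section says: "The Vascular Assessment Nurse who provides usual care at diagnosis, and who recruits participants, will be blind to participant allocation to groups". The nurse sends names to the researcher, who allocates from a random number table before any contact with the patient. No stratification or minimisation is described.
- **What determines treatment.** The Usual Care section says: "Appropriate treatment depends on the age and health of the patient, the size and location of the narrowing of the artery". The same sentence adds the patient's wishes. ABPI is not in the list. The only stated link between ABPI and surgery is in the Exclusion Criteria: "Patients with an ABPI of less than 0.35 will also be excluded as they are likely to be offered emergency surgery".

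**The concern.** The plan already holds a variable that it says affects the treatment decision (age) and one that plausibly reflects severity (ABPI). Both are obtained at diagnosis, before the researcher allocates, by someone who cannot know the arm, so they are safe covariates that need no new measurement. The walking outcome at least enters a group-by-time analysis that contains its own baseline value. Surgery uptake has no baseline value, so under the stated test its comparison uses no baseline information at all.

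In a single trial of about 60 patients the arms may differ by chance in age or severity. If they do, the unadjusted difference in uptake moves with that imbalance, and it is this one estimate that would be carried into planning the larger trial. Choosing covariates only after the imbalance has been seen would be open to criticism, so the time to name them is beforehand.

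**Working it through.** **Inputs from the protocol article.** 60 recruited and 6 expected to drop out, leaving 54, or 27 to 30 per arm (Recruitment); about 56% proceed to angioplasty or surgery (Usual Care); chi-square test (Analysis). **Assumed, because the documents give no figure:** how strongly the covariates predict surgery.

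**The plan's own figure.** No figure is given for surgery uptake; the trial is sized on walking. The stated 26 per arm reproduces for a 2 × 2 mixed ANOVA with effect size f = 0.2 and an assumed correlation of 0.5 between time points: N = 52 gives power 80.7%, N = 50 gives 79.1%.

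**1. Precision of the unadjusted comparison.** SE = √(0.56 × 0.44 × 2/n). With n = 30 this is 12.8 percentage points, 95% half-width 1.96 × 12.8 = 25 points. With n = 27 it is 13.5 points, half-width 26 points. Power at 30 per arm for 56% versus 36% is about 34%.

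**2. Expected chance imbalance.** The between-arm difference in a standardised covariate has SD √(2/n): 0.26 at n = 30 and 0.27 at n = 27. At n = 30, the probability of an imbalance above 0.25 SD is 33% and above 0.5 SD is 5%; at n = 27 these are 36% and 7%.

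**3. Shift in the uptake difference, by formula.** If the covariates explain a share R² of the variation in who has surgery, the shift exceeded in 1 trial in 20 is 1.96 × √(2/n) × √R² × √(0.56 × 0.44).

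- R² = 0.10: 7.9 points (n = 30) to 8.4 points (n = 27)
- R² = 0.20: 11.2 to 11.8 points

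**4. Shift and precision, by simulation.** 4,000 trials per setting, 30 per arm, 56% uptake in both arms, one standardised covariate. The unadjusted difference is compared with the standardised risk difference from a logistic model. Figures are percentage points.

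| Assumed odds ratio per SD | Shift at a 1-SD chance imbalance | SD unadjusted | SD adjusted | Change in SD |
|---|---|---|---|---|
| 1.0 | 0.0 | 12.8 | 13.0 | +1% |
| 1.5 | 2.5 | 12.8 | 12.6 | −1% |
| 2.0 | 4.0 | 13.0 | 12.5 | −4% |
| 3.0 | 5.6 | 12.9 | 11.7 | −10% |

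Multiplying the shifts by 1.96 gives 4.9, 7.8 and 11.0 points at odds ratios 1.5, 2 and 3. The last two agree with step 3. After adjustment the estimate no longer depends on the imbalance (slope about 0).

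**5. Validity of the stated test.** The chi-square type I error was 5.2% to 5.3%, and the unadjusted estimate was unbiased on average. Imbalance contributes (2.5/12.8)² = 4%, (4.0/13.0)² = 9% and (5.6/12.9)² = 19% of its sampling variance at odds ratios 1.5, 2 and 3.

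**6. Power at 56% versus 36%,** unadjusted to adjusted: 34% to 34%, 36% to 38% and 36% to 41% at the same odds ratios.

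**7. Can the model be fitted?** Non-surgery participants: 0.44 × 60 = 26, or 0.44 × 54 = 24. With arm, age and ABPI that is about 8 to 9 per parameter.

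**The case against.** The strongest reply is that nothing here is an error. A chi-square test after simple randomisation is legitimate, its error rate is correct, and chance imbalance is already part of its standard error. Unstratified allocation is also legitimate. Sample size dominates: the half-width of about 25 points hardly changes unless the covariates are strongly prognostic, and a covariate with no prognostic value slightly widens it. The Analysis section is short, and covariates are often left to an analysis plan. All of this stands as a limit on the size of the point. It does not dispose of it, because the article does not leave the method open: it names an unadjusted test for this outcome, while elsewhere it names age as a determinant of treatment and holds the value.

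Two stronger readings are tempting and should not be drawn.

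- A reader might infer that the surgery comparison is biased or invalid. The documents and the simulation do not support that. The bias is conditional on the imbalance that happens to occur, and averages to zero over repeated randomisation.
- A reader might infer that ABPI drives the choice of surgery. No section says so. Usual Care lists age, health, the size and location of the narrowing, and the patient's wishes. The exclusion below 0.35 does link ABPI to surgery, but with the diagnostic criterion of "post-exercise ABPI of below 0.9" it also narrows the range of ABPI among participants, which may weaken its prediction. Even for age, no direction or strength is given.

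There are practical objections too. Retention of the values depends on verbal consent, and disease in one or both legs is eligible, so ABPI needs a definition.

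**Conclusion.** The point holds as a modest improvement to a stated method. The planned test is sound on average, but it leaves the surgery estimate exposed to imbalance that data already collected could remove. If the covariates are moderately to strongly prognostic (odds ratio 2 to 3 per SD, or R² of 0.10 to 0.20), chance imbalance moves the difference by about 8 to 12 percentage points or more in 1 trial in 20; at an odds ratio of 1.5 it is about 5 points. The average gain from adjustment is a 1% to 10% lower SD of the estimate over odds ratios 1.5 to 3. These figures rest on assumed prognostic strength and on 56% uptake; the simulation used a single covariate standing in for age and ABPI. Adjustment will not turn the pilot into an informative test of surgery uptake. It will give the larger trial an effect estimate that does not depend on the imbalance in age and ABPI that happened to arise.

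**What to change.** In the Analysis section, prespecify a comparison of surgery uptake from a logistic model with arm, age and ABPI as recorded at diagnosis, reported as a standardised risk difference with its 95% confidence interval. Keep the chi-square test alongside it. State which ABPI enters the model when both legs are affected.

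The cost is a sentence or two and no new data. The model spends two extra parameters on a sample with about 24 to 26 non-surgery participants, which is workable but not generous. If age and ABPI predict surgery only weakly, the gain will be negligible, and with no prediction at all the SD rises by about 1%.
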